## Secondary Objectives:

1. To evaluate the reasons and the process of each step of the changes in treatment regimen during the 12-month follow up.
2. To evaluate the influential factors related to the changes of the treatment patterns for newly diagnosed T2D, including clinical outcomes, pattern of blood glucose monitoring, social-economical status (i.e. insurance status, income status, education background, etc), patients’ compliances, patients’ knowledge of diabetes, hospital tier, specialties of the physicians;
3. To assess the incidence of CVD risk factors (i.e. hypertension, lipidemia and obesity) and the intervention patterns;
4. To assess the associated incidence of diabetic complications, including cardiovascular / cerebrovascular and microvascular diseases;
5. To assess the application of diabetes related clinical examinations such as Fundus examination and diabetic foot screening;
6. To assess the methods of diagnosis (i.e. routine physical examination, health screening, seeking health care due toT2D symptoms, seeing doctors for other diseases, etc), and location of diagnosis (i.e. the tier of hospital, the physician specialty, etc) and the influential factors.
7. To assess the incidence of hypoglycemia and other AEs and SAE, that may be related to anti-diabetes medications.
8. To access the medical resource consumption pattern for treating diabetes.
9. To evaluate the health conditions and quality of life at the baseline and at the 12th month.

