- Hypoglycemic symptoms and severity: Hypoglycemia is defined as the fasting plasma glucose level below 70 mg/dL according to the American Diabetes Association 2009 Position Statement [12]. The symptoms of hypoglycemia include but not limited to sweating, hunger, trembling, anxiety, confusion, blurred Vision. A simple questionnaire will be used to record patient reported symptoms and severity.
- Lab tests: Blood tests should be performed after fasting for at least 10 hours.
- Serum glucose: The oxidase method should be used;
- HbA1C: It should be determined by high performance liquid chromatography (HPLC)
- Lipid panel: TC – total cholesterol, LDL-C – low density lipoprotein, TG – triglyceride, HDL-C – high density lipoprotein
- Kidney function: serum creatinine
- Liver function (Gamma-GT, ALT, AST)
- Urine test (urine albumin, creatinine or albumin / urine creatinine ratio)

Notice: Lipid panel and liver function are tested every 6 months, while other lab tests are conducted every 3 months.

If any additional diagnose test is ordered as part of the routine medical course, a copy of the results should be obtained. Any change of medical history, hospitalization, and medication will be specially noted (cause, dosage, outcome, etc). Unsolicited safety reports on products marketed by Bristol Myers Squibb will be collected.

Lab test methods:

- - - All blood samples should be venous blood after at least10-hour fasting;
    - HbA1c should be tested using high performance liquid chromatography (HPLC) method;
    - Fasting blood lipids: total cholesterol, triglycerides, high density lipoprotein, low density lipoprotein;
    - Urinalysis: 24 hours urine, short time urine, or random urine are accepted;
    - Albumin to creatinine ratio: urine (3-4 ml) measured within two hours after collection. Urine albumin is tested using immune turbidimetric method. Urine creatinine is tested using oxidase method.
- In addition to the scheduled follow-up visits of NEW2D and the information collected at each visit, the extra visits of the patients should also be briefly recorded, including the date, the reason (needed prescription, needed treatment), having tested for blood glucose, method of the test and the results if available;
- Adverse events: gastrointestinal reactions, edema, weight gain, change of liver or kidney functions, allergic, other discomforts (details);
- Severe adverse events: for BMS products only.

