## Study Flow Chart

| **Procedure** | **Baseline Visit** | **Follow Up Visits (3, 6, 9, and 12 months after baseline visit +/- one month)^g^** |
| --- | --- | --- |
| Inclusion/Exclusion Criteria | X |  |
| Written informed consent form | X |  |
| Demographic Data ^a^ | X |  |
| Diabetes history | X |  |
| Family history | X |  |
| Medical history and co-morbidity ^b^ | X | X |
| Knowledge about T2D | X | X |
| Health behavior ^c^ | X | X |
| Physical Exam^d^ | X | X |
| Medication ^e^ | X | X |
| Hypoglycemic symptoms and severity | X | X |
| Laboratory tests ^f^ | X | X |
| Unsolicited safety report ^h^ | X | X |
| Self-evaluated life quality ^i^ | X | X |

1. Demographic data include age, gender, residential region, educational level, and social-economic status.
2. Including cardiovascular event and other complication occurred as medical history or during follow up.
3. Including smoking history and exercise pattern.
4. Including height, body weight, waist circumference, blood pressure
5. Current and any change of medications since last recorded visit for treatment of type 2 diabetes, diabetic complications, lipid-regulation, and hypertension, including prescription drugs, OTC drugs and Chinese herbal medicines with their names and doses.
6. Laboratory tests include: fasting blood glucose, HbA1c, fasting blood lipid (TC, HDL-C, LDL-C, and TG, tested every 6 months), liver function (every 6 months), kidney function (serum creatinine), and urine analysis (microalbumin/albumin, urine creatinine, or albumin to creatinie ratio).
7. An one month time window is permitted for each follow up visit.
8. Adverse events include gastrointestinal reactions, edema, weight gain, liver and kidney function, allergies, etc.
9. Unsolicited safety reports on products marketed by the BMS will be collected, then reported to health bureau and BMS
10. EQ-5D questionnaire will be applied.

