## Definitions of adverse events

**Adverse Event (AE)** is any untoward medical occurrence in a patient or clinical investigation subject administered a pharmaceutical product and which does not necessarily have to have a causal relationship with this treatment.

Therefore, an adverse event can therefore be any unfavourable and unintended sign (including an abnormal laboratory finding, for example), symptom, or disease temporally associated with the use of a medicinal product, whether or not considered related to the medicinal product.

**Serious criteria,** one of the following reactions caused by using the medical product:

1. Results in death;
2. Is life-threatening;
3. Requires inpatient hospitalization or causes prolongation of existing hospitalization;
4. Results in persistent or significant disability/incapacity;
5. Is a congenital anomaly/birth defect;
6. Is an important medical event (defined as a medical event(s) that may not be immediately life-threatening or result in death or hospitalization but, based upon appropriate medical and scientific judgment, may jeopardize the patient/subject or may require intervention (e.g. medical, surgical) to prevent one of the other serious outcomes listed in the definition above.)

Adverse Event Reporting

| **Drugs** | **Description of report** | **Timeframe (calendar day)** | **Transmission** |
| --- | --- | --- | --- |
| Imported drugs within 5 years of first approved in China  (For example Onglyza) | Death | Immediately | Fill out the “Drug Adverse Reaction/Event Report Form”   - **Online** report: [www.adr.gov.cn](http://www.adr.gov.cn)   <Note^[[1]](#footnote-0)^>  Or   - Fax/Email: XXXXXXXX (*ADR Canter where the hospital located)*   <Note^[[2]](#footnote-1)^> |
|  | Serious or unexpected ADR | Within 15 days |  |
|  | Other ADRs | Within 30 days |  |
| Drugs beyond observation period/ imported drugs beyond 5 years of first approved in China  (For example Glucophage, Monopril) | Death | Immediately |  |
|  | Serious or unexpected ADR | within 15 days |  |

IMPORTANT:

1. Death cases shall be reported immediately.
2. Follow-up visits, if any, shall be reported promptly.

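### SAEs are recorded only for the funder's products, so the SAE part of secondary objective 7 cannot be answered for other anti-diabetes drugs

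*Protocol*

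**What the plan says.** Protocol Section 3.2, item 7, repeated in the synopsis, sets this objective: "To assess the incidence of hypoglycemia and other AEs and SAE, that may be related to anti-diabetes medications". It names no manufacturer.

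Section 5.2 lists what is recorded at baseline and follow-up. Three items bear on the objective:

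- Hypoglycemia, with no product limit: "A simple questionnaire will be used to record patient reported symptoms and severity".
- Ordinary adverse events, with no product limit: "Adverse events: gastrointestinal reactions, edema, weight gain, change of liver or kidney functions, allergic, other discomforts (details").
- The next bullet, which does carry a limit: "Severe adverse events: for BMS products only".

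A note to the flow chart in Section 5.3 has the same limit for spontaneous reports: "Unsolicited safety reports on products marketed by the BMS will be collected, then reported to health bureau and BMS".

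Section 10.2 first defines an adverse event without requiring a causal link to treatment. It then introduces the seriousness criteria as "one of the following reactions caused by using the medical product".

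**The concern.** The objective covers all anti-diabetes drugs, while the collection rule for its gravest component covers one company's drugs. This is a rule about data capture, so a statistical analysis plan cannot repair it: events that were never entered cannot be recovered in analysis.

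Three consequences follow for the SAE item. Other manufacturers' drugs have no SAE numerator. An overall SAE incidence computed from the item over the whole cohort is too low. If someone tabulates SAEs by drug, the events cluster on the funder's products because only those were asked about.

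The wording adds a second difficulty. Section 5.2 says *severe* where Section 10.2 defines *serious*, so a site cannot be sure which concept is meant. The definition in 10.2 also makes causality part of seriousness. An event judged unrelated could then fall out before it is counted, although objective 7 asks about events that may be related, which is a wider set.

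**Working it through.** The Protocol gives no SAE figure to reproduce, so the main check sets its sections side by side.

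**Step 1. Objective against collection.**

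| Component of objective 7 | Scope of the objective | Scope of collection (Section 5.2) | Answerable? |
| --- | --- | --- | --- |
| Hypoglycemia | any anti-diabetes drug | all patients | yes |
| Other AEs | any anti-diabetes drug | listed types, no product limit | yes |
| SAEs | any anti-diabetes drug | funder's products only | not for other drugs |

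**Step 2. Does another section fill the gap?**

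- Section 10.1 sends study-connected adverse events to the regulator, and events on the funder's products to the funder. These are reporting routes. Neither places other drugs' SAEs in the study data.
- The flow chart adds only unsolicited reports on the funder's products.
- Section 5.2 also says: "Any change of medical history, hospitalization, and medication will be specially noted (cause, dosage, outcome, etc"). This applies to every patient, and hospitalization is one of the seriousness criteria in Section 10.2. No suspect drug or seriousness classification is asked for.
- A flow-chart note widens medical history: "Including cardiovascular event and other complication occurred as medical history or during follow up". This too covers every patient, again without a suspect drug or seriousness assessment.
- Two criteria in Section 10.2, lasting disability and important medical events, are not named among the Section 5.2 items.

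The gap is therefore partly covered by proxy and not closed.

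**Step 3. How large could the gap be?** This is an illustration. Let N be the number of patients, r the true risk of a drug-related SAE (one per patient, equal on all drugs), and s the share of patients on the funder's products. Then:

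- true SAEs = N × r
- SAEs in the item = N × r × s
- apparent cohort incidence = r × s
- captured fraction = (N × r × s) / (N × r) = s

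N = 3,945 is the number before the attrition allowance in Section 7 (1,315 × 3). Both r and s are assumptions, because the Protocol gives neither. With r = 3%, true SAEs = 3,945 × 0.03 = 118.

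| s (assumed) | SAEs in the item | Apparent incidence (true 3%) | Missed |
| --- | --- | --- | --- |
| 5% | 5.9 | 0.15% | 95% |
| 10% | 11.8 | 0.30% | 90% |
| 20% | 23.7 | 0.60% | 80% |
| 30% | 35.5 | 0.90% | 70% |
| 50% | 59.2 | 1.50% | 50% |

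At r = 1% (39.5 true SAEs), the item holds 2.0 to 19.7 events as s runs from 5% to 50%. At r = 5% (197.2 true SAEs), it holds 9.9 to 98.6. The fraction missed is 1 − s whatever r is. If risk differs between drugs, the captured fraction is instead the share of SAEs that arise on the funder's products.

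**The case against.** The strongest reply is that the damage is narrow, and most of that reply stands.

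A reader might infer that objective 7 as a whole cannot be answered. The Protocol does not support this, since hypoglycemia and the listed AEs are collected for everyone.

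A reader might also infer that every between-drug comparison is biased. That goes too far. Section 6.2 lists no SAE endpoint and specifies no SAE comparison by drug. Its drug-safety endpoint is hypoglycemia by anti-diabetic treatment, which this restriction does not touch, and Section 7 describes a descriptive study without hypothesis tests. The distortion would arise only if SAEs were tabulated by drug.

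Nor is it right that the study data hold nothing serious for other drugs. Besides hospitalizations and cardiovascular events, Section 5.2 records medication and adverse events as a reason for changing treatment. Because combination regimens are expected (Section 6.2), a patient taking a funder's product together with another drug is not clearly outside the SAE item. The zero applies to the dedicated item and to drugs taken without a funder's product.

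The flow chart is weaker support than Section 5.2. Its superscripts run to nine letters against ten notes, and the letter on the safety-report row points by count to the general adverse-event note, which has no product limit.

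Finally, Section 10.2 belongs to the reporting chapter and is not shown to govern eCRF entry. Its conflict with the AE definition is real, but it does not by itself prove that incidence data are lost.

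None of this removes the conflict between the SAE words of objective 7 and the rule in Section 5.2.

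**Conclusion.** The point holds for the SAE component of one of the nine secondary objectives. As written, SAE incidence cannot be estimated for other manufacturers' drugs, cohort SAE incidence from the SAE item would be understated, and any SAE tabulation by drug would reflect differential ascertainment. Hospitalizations and cardiovascular events give a partial check only.

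The size is unknown because the Protocol does not state the share of patients on the funder's products. The 50% to 95% range for missed events rests on an assumed share of 5% to 50% and equal SAE risk across drugs. It describes the SAE item alone and ignores the proxy data, so it should not be read as an estimate for this cohort.

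The primary endpoint, the hypoglycemia and other-AE parts of objective 7, and the hypoglycemia endpoint are unaffected. The change should be made because a plan followed as written would give a wrong SAE incidence that later analysis could not correct.

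**What to change.** **Preferred.** In Section 5.2, record serious adverse events for every patient on any anti-diabetes medication, with event, date, suspect drug and outcome. Keep expedited transmission to the funder for its own products only. The cost is modest but goes beyond a form change: extra eCRF entry, training at about 80 hospitals, and ethics review of the changed documents. Visits, medication records, AE items and causes of hospitalization are already collected.

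**Otherwise.** Limit only the SAE words of objective 7, in the synopsis and Section 3.2, to the funder's products, and state that no SAE comparison with other drugs will be made. Leave the hypoglycemia and AE parts unchanged. Narrowing the whole objective would discard usable data and clash with the hypoglycemia endpoint. This option costs a wording change and gives up SAE incidence for other drugs.

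**In either case.** Use the single term *serious* in Sections 5.2 and 10.2. In 10.2, define seriousness by outcome and record causality as a separate item, so that it agrees with the AE definition above it and with the possible-relatedness wording of objective 7. Align the flow-chart notes in 5.3 and the reporting text in 10.1 with the option chosen.

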## Study Flow Chart

| **Procedure** | **Baseline Visit** | **Follow Up Visits (3, 6, 9, and 12 months after baseline visit +/- one month)^g^** |
| --- | --- | --- |
| Inclusion/Exclusion Criteria | X |  |
| Written informed consent form | X |  |
| Demographic Data ^a^ | X |  |
| Diabetes history | X |  |
| Family history | X |  |
| Medical history and co-morbidity ^b^ | X | X |
| Knowledge about T2D | X | X |
| Health behavior ^c^ | X | X |
| Physical Exam^d^ | X | X |
| Medication ^e^ | X | X |
| Hypoglycemic symptoms and severity | X | X |
| Laboratory tests ^f^ | X | X |
| Unsolicited safety report ^h^ | X | X |
| Self-evaluated life quality ^i^ | X | X |

1. Demographic data include age, gender, residential region, educational level, and social-economic status.
2. Including cardiovascular event and other complication occurred as medical history or during follow up.
3. Including smoking history and exercise pattern.
4. Including height, body weight, waist circumference, blood pressure
5. Current and any change of medications since last recorded visit for treatment of type 2 diabetes, diabetic complications, lipid-regulation, and hypertension, including prescription drugs, OTC drugs and Chinese herbal medicines with their names and doses.
6. Laboratory tests include: fasting blood glucose, HbA1c, fasting blood lipid (TC, HDL-C, LDL-C, and TG, tested every 6 months), liver function (every 6 months), kidney function (serum creatinine), and urine analysis (microalbumin/albumin, urine creatinine, or albumin to creatinie ratio).
7. An one month time window is permitted for each follow up visit.
8. Adverse events include gastrointestinal reactions, edema, weight gain, liver and kidney function, allergies, etc.
9. Unsolicited safety reports on products marketed by the BMS will be collected, then reported to health bureau and BMS
10. EQ-5D questionnaire will be applied.

# OBSERVING ENDPOINTS

## Primary endpoints

The overall proportion of patients whose HbA1c is less than 7%, measured at the end of one year follow up.

## Secondary endpoints

The secondary endpoints of this study include the following;

1. The proportions of patients receiving one OAD, two OADs, > two OADs, insulin alone, insulin+one OAD, insulin+two OADs, insulin+>two OADs and by class of OADs at 3, 6, 9, and 12 months;
2. Mean duration of diet & exercise alone (t_4_), initial anti-diabetic treatment (ADT) (t_1_), initial ADT is switched or 2^nd^  ADT is added (t_2_), 2^nd^ ADT is switched or 3^rd^ ADT is added (t_3_) ; (Figure 1 Treatment Pattern Diagram);
3. The proportion of patients reached the therapeutic target of glycemic control by treatment regimen and by OAD class at 3, 6, 9 and 12 months:
4. The correlation between treatment patterns and patient demographics, social-economic status, insurance, medical history, HbA1C level, type of hospital, physician years of practice, etc;
5. Incidence of microvasular diabetic complication: diabetic retinopathy, nephropathy, neuropathy, and macrovascular complications: cardiovascular events, peripheral vascular complications, and stroke, at 3, 6, 9, and 12 months;
6. Were the diabetes related clinical examinations applied such as Fundus examination and diabetic foot screening;
7. Incidence of hypoglycemia associated with various ADTs;
8. Diagnosis pattern: to assess the methods of diagnosis (i.e. routine physical examination, seeing doctors for other diseases, etc), and location of diagnosis, demographic information of the patients and the regions of residence;
9. Quality of life assessment (baseline and the last visit);
10. Resource consumption patterns based on the information collected on the cost of medications, cost of diagnostic test and other relevant [procedure.

Figure 1 Treatment Pattern Diagram

[figure not shown]

T1 = duration between diagnosis and initiation of (single) treatment regime， T2 = duration between initiation of single treatment regime and duple regime， T3 = duration between initiation of duple treatment regime and multiple regime

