# STUDY OBJECTIVES

## Primary Objectives:

To assess the evolution of treatment patterns for newly diagnosed T2D patients and the clinical outcomes during a 12-month follow up.

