# STUDY DESIGN

## General design

Any newly diagnosed (within 6 months) type 2 diabetic patient who is visiting tier 3, 2, or 1 hospitals, may be considered for enrollment in this study, as long as the patient meets the inclusion and exclusion criteria and is willing to sign on the informed consent form.

Enrolled patients will receive routine treatment (diet & exercise or medication) and will be asked to return to the same investigator for follow up visits at 3, 6, 9 and 12 month after the baseline visit.

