# STUDY PROCEDURE

## Baseline Measurements

- Demography: Age, gender, residential region.
- Diabetes history and related symptoms: Duration or diagnosis (must be < 6 months), how was diagnosis made (using the 2010 Chinese Guideline for Diabetes Prevention and Treatment [19]) , signs and symptoms.
- Diagnostic pathways:
  1. Seeking health care due to diabetic symptoms
  2. Already found an increased blood glucose once, and confirmed by a second test
  3. Seeking health care due to other diseases
  4. Self-demanded lab tests
  5. Participating in an epidemiological study / campaign
- Screening methods for diabetes (could be singular or multiple choices):
  1. OGTT test
  2. “Bun test”
  3. Urine glucose
  4. Others
- Diagnostic methods for diabetes* (reference table 1), diabetic symptoms plus:
  1. Random blood glucose (the blood glucose level at any time during a day without knowing the time of last meal)
  2. FBG (fasted for at least 8 hours without calories intake)
  3. 2-hour postprandial blood glucose
- Diabetics symptoms: thirsty, constant hunger, frequent micturition, obvious weight loss, fatigue, prone to inflammation, blurred vision, numbness/pain, leg or foot ulcers, skin itching, acute complications such as ketosis, hyperosmolar coma, *etc.*
- The hospitals and departments where diabetes was diagnosed:
  1. Tier 1 hospital
  2. Tier 2 hospital: endocrinology dept., internal medicine dept.
  3. Tier 3 hospital: endocrinology dept., internal medicine dept.
- Disease history:
  1. Diabetic complication history: the acute or chronicle diabetic complications at or after the diagnosis, including ketosis, hyperosmolar coma, HHS, micro blood vessels lesions (retinal lesions, nephrological diseases, peripheral neuropathy).
  2. Medical history and co-morbidity: Including any major medical procedure or surgery occurred within the last 12 months, any major co-morbidity (e.g. cardiovascular disease, renal disease, other diabetic complications, cancer, etc).
- Family history: Family history of diabetes and cardiovascular diseases
- Education level and knowledge about T2D: Highest formal education received as well as response to simple questionnaire assessing the level of knowledge about T2D.
- Social-economic background: Employment status, marital status, monthly income, insurance type and coverage.
- Questionnaire for diabetes knowledge assessment
- Quality of life assessment (repeated at the last visit)

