## Measurements at Baseline and Follow-up Visits

Each patient will return to see the same physicians for follow up visits at 3, 6. 9 and 12 month after the first visit, and the following measurements will be recorded, laboratory reports will be obtained.

- Blood pressure: The subjects should be resting for at least 5 minutes prior to measurement of blood pressure. Measure the sitting or supine blood pressure, and take the mean of values of 2 continuous measurements. There should be 2 minutes interval between the 2 measurements.
- Height and body weight: Remove the shoes and socks prior to measurement, as well as wear light clothes. Formula for body mass index calculation: BMI= Body weight (kg)/Body height^2^ (m)
- Waist circumference: Remove the clothes on the waist and stand relaxed with both hands down naturally. Then use tape around the waist and adjust its location to make the tape pass the intermediate points between superior margins of hip bones at both sides and lower costal margins. Pay attention to that the tape should be parallel to the floor and cling to but no compress the skin.
- Health behavior
- Smoking history: Record the average number of cigarettes per day and smoking time. A smoker is defined as a person who smokes 1 cigarette a day on the average for at least 1 year.
- Exercise pattern: Physical inactivity means the subjects do not have frequent physical exercise (such as amount of exercise equal to that in walking for at least 20-30 minutes a day, 3-4 days a week).
- Medication: Including medication previously prescribed for glycemic control and any other concurrent medications. Record generic name, brand name, dosage, frequency, years taken, and purpose. Current and any change of medications since last recorded visit for treatment of type 2 diabetes, diabetic complications, lipid-regulation, and hypertension, including prescription drugs, OTC drugs and Chinese herbal medicines should be recorded.
- Reason for adjusting anti-diabetic medications
  1. Unsatisfactory treatment outcomes: according to FBG results, or 2-hour postprandial blood glucose, or HbA1c
  2. Adverse events: hypoglycemia, gastrointestinal reactions, edema, weight gain, change of liver or kidney functions, allergic, other discomforts.
  3. Economical reasons
  4. Self-adjustment: details will be required
- Compliances: does the patient routinely take medicines in accordance with the prescriptions, if not, the specific reasons will be required

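### The diagnostic pathways recorded at baseline omit routine physical examination, the method that objective 6 and endpoint 8 name first; as a minor point, endpoint 1 has no row for patients on no drug

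*Protocol*

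**What the plan says.** **Method of diagnosis.** Secondary objective 6 (section 3.2 and synopsis) asks how diabetes was found. It names routine physical examination first, then health screening, symptoms and visits for other diseases. Endpoint 8 in section 6.2 repeats the aim: "to assess the methods of diagnosis (i.e. routine physical examination, seeing doctors for other diseases, etc". The item to be recorded is the Diagnostic pathways list in section 5.1, whose five options are, in paraphrase:

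1. care sought because of symptoms
2. a raised glucose found before and verified on repeat
3. care sought for another disease
4. a test the patient asked for
5. "Participating in an epidemiological study / campaign"

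The list ends there.

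**Treatment pattern.** Endpoint 1 in section 6.2 reports "The proportions of patients receiving one OAD, two OADs, > two OADs, insulin alone, insulin+one OAD, insulin+two OADs, insulin+>two OADs". A breakdown by drug class is added, and the time points are months 3, 6, 9 and 12. Section 4.1 says "Enrolled patients will receive routine treatment (diet & exercise or medication", and endpoint 2 includes "Mean duration of diet & exercise alone (t_4". The primary objective (section 3.1) is "To assess the evolution of treatment patterns for newly diagnosed T2D patients" together with clinical outcomes. Medication is recorded at baseline and at each follow-up visit (sections 5.2 and 5.3), "Including medication previously prescribed for glycemic control and any other concurrent medications".

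**The concern.** A category list has to hold every group that the matching endpoint promises to count. The pathway list does not, and the missing group is the one its own objective mentions first. This is a question of data capture. How a patient came to be diagnosed is asked once, at baseline, so a route that was not offered then cannot be restored at analysis. Someone whose diabetes was found at a check-up has no fitting answer and may be entered under another pathway, which blurs that pathway as well.

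Endpoint 1 has a milder gap of the same kind. Its categories are all drug regimens, although the protocol elsewhere treats diet and exercise alone as a treatment state, and its time points begin at month 3 although the objective concerns change over the year. Here the underlying data are collected, so only the presentation is at stake.

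**Working it through.** The point rests on comparing lists. The plan gives no figure for how many patients are found at a routine examination or take no drug.

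**Step 1: methods named against options recorded.**

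| Method named in objective 6 or endpoint 8 | Matching option in section 5.1 |
| --- | --- |
| Routine physical examination | none |
| Health screening | at best part of option 5 |
| Symptoms of diabetes | option 1 |
| Seen for another disease | option 3 |
| Open-ended remainder | option 4; no open option |

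Option 2 matches no named method. It describes how a raised value was confirmed, and that can follow any route of detection. It is therefore a likely place for a check-up finding to be entered, where it would be mixed with patients detected in other ways. In the same section, the list of screening methods has an open option and says whether several answers are allowed. The pathway list does neither.

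**Step 2: size.** Let r be the share of patients found at a routine examination. Collected as listed, the reported share for that route is absent instead of r, and up to r is spread over the other options. The planned enrolment in section 7 is 1,315 × 3 = 3,945, and 3,945 / 0.80 = 4,931.25, stated as 4,931. One percentage point of r is then 0.01 × 4,931 ≈ 49 patients.

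**Step 3: what endpoint 8 still delivers.** Section 5.1 collects the tier and department where the diagnosis was made, age, gender and residential region, as well as the other pathways. Only the routine-examination share is lost, and the pathways that absorb those patients are contaminated.

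**Step 4: endpoint 1.** The seven categories are three with OADs only, one with insulin alone and three with insulin plus OADs. None is drug-free. Let s be the share of patients in none of the seven. The documents do not give s, so the range below is an assumption, applied to the 3,945 evaluable patients.

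| s (assumed) | Sum of the seven shares, 1 − s | Patients outside, s × 3,945 |
| --- | --- | --- |
| 5% | 95% | 197 |
| 10% | 90% | 394 |
| 20% | 80% | 789 |
| 30% | 70% | 1,184 |

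With patients as the denominator, this remainder is mostly the group on diet and exercise alone. It would also hold anyone on herbal medicine only, which sections 5.2 and 5.3 record but endpoint 1 does not place.

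**The case against.** On endpoint 1 the defence largely succeeds. The endpoint is stated over patients, medication is recorded at every visit, and nothing excludes patients on no drug, so the untreated share is close to the remainder. Endpoint 2 reports time on diet and exercise alone. Baseline regimen is collected, section 7 says baseline characteristics will be summarised, and an analysis of baseline data is planned when enrolment ends. A reader might infer that the first treatment change is hidden, but it can be shown from these data. A reader might also infer that the listed shares are inflated by 1/(1 − s), that is by 1.11 at s = 10% and 1.43 at s = 30%. That requires rescaling to treated patients, which the protocol nowhere proposes. Endpoint 1 is also formally secondary; the primary endpoint is the HbA1c proportion.

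On the pathway list the defence is partial. It is tempting to say that endpoint 8 cannot be estimated at all, or that every patient found at a check-up is misclassified. The first fails because location, demographics, region and the other routes are still captured. The second assumes a compulsory, closed, single-answer item; section 5.1 does not say that, and the eCRF is not shown. For the same reason, the documents do not require a single-choice rule. A check-up finding could be entered under option 2, and a screening finding under option 5. That loses detail without necessarily being wrong, but it still leaves the first-named method unidentifiable, and that part of the concern stands.

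**Conclusion.** The section 5.1 pathway list does not match secondary objective 6 and endpoint 8. Routine physical examination is named first in both and cannot be recorded as such, and there is no open option to catch it. Its share cannot be separated from data collected as listed, nor recovered afterwards. The loss is about 49 of 4,931 planned patients for each percentage point detected this way; the true share is unknown. This assumes that the eCRF follows the protocol's list.

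The missing no-drug category in endpoint 1 is a minor clarification. It concerns the naming of a remainder and the display of baseline, and the data for both are already recorded. Neither part touches the primary endpoint or the sample size.

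**What to change.** **Section 5.1, Diagnostic pathways:** add routine physical examination, health screening and an open other option, so that the list covers what objective 6 and endpoint 8 name. Record confirmation by a second test as its own item, separate from the route of detection. This should be done before enrolment, because the item is asked only at baseline.

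**Section 6.2, endpoint 1 (clarification):** add one category for no anti-diabetic drug (diet and exercise alone) and one for other treatment, such as herbal medicine only. State that the denominator is all patients seen at the visit. Show the baseline regimen beside months 3, 6, 9 and 12.

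The cost is a few eCRF response options and some table rows. No additional visit, test or patient is needed.
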